#### Statistical analysis

Continuous variables will be assessed for normality and expressed as mean (SD) or median (IQR), depending on the underlying distribution of the data. Categorical variables will be reported as counts and proportions. Differences in physiological values between survivors and non-survivors will be interrogated with the Mann-Whitney U test for non-normally distributed continuous variables, Student’s t-test for normally distributed continuous variables and Fisher’s exact test for categorical variables. All tests will be two tailed and unadjusted for multiple comparisons. Spearman rank correlation coefficient (ρ) will be used to see correlations between variables. Identification of critical threshold values of PRx for predicting unfavourable outcome will be performed using iterative χ^2^ tests, as per the method described by Sorrentino *et al*.^21^ To account for any possible confounding effect of the differing periods of monitoring and day post admission on which monitoring starts on outcome associations, ordinal logistic regression analysis will be performed. The independent effect of each continuously monitored variable on GOSE-Peds will be assessed by including the length of monitoring and monitoring commencement day post admission as covariates in the regression models. Where appropriate PRx will be Fisher transformed to remove the <−1; 1> constrain and ensure normalisation of its distribution. The effect of time on PRx will be assessed using repeated-measures analysis of variance with each patient treated as a random effect.

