### Study objectives

Primary objective: To detect thresholds of PRx associated with favourable outcome in PTBI.

Secondary objectives:

Characterise patterns of CPPopt in PTBI as a function of age, severity and character of injury, ICP, etc.Compare the fluctuations in these measured parameters with the outcome.Establish a comprehensive paediatric database of a basic set of high resolution (pulse waveforms resolution) neuromonitoring data including ICP, ABP and ECG.

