### Outcome measures

The primary outcome will be measured by Glasgow Outcome Scale Extended Paediatric version (GOSE-Peds) at 12-month postinjury against the PRx.

The study will also include the following secondary outcome measures:

GOSE-Peds at 6 months against the PRx.Delta CPP (CPP deviation from CPPopt) against the GOSE-Peds at 6 and 12 months.Rate of severe TBI-related surgical interventions undertaken during the index admission.Mortality (30 days, 6 months 12 months).Length of stay in hospital and rehabilitation.

There is more detailed neuropsychology assessment at 12 months follow-up by using telephone-based interviews and postal questionnaires with parents by using the following tests (child versions will be used where available): Behaviour Rating Inventory for Executive Function (BRIEF), Pediatric Quality of Life Inventory (PedsQL), Strengths and Difficulties Questionnaire (SDQ), Children’s Communication Checklist (CCC), Child and Adolescent Scale of Participation (CASP) and Revised Children’s Anxiety and Depression Scale (RCADS). In addition, with parental permission, school teacher will be contacted for SDQ and BRIEF with postal questionnaires.

Due to the covid-related impact on research, to circumvent the missed follow-ups for the recruited patients:

Where possible, site teams will carry out telephone interview with parents/legal guardian to ascertain child’s neurodevelopmental performance at the first anniversary of child’s head injury for retrospective GOSE-Peds score at 12 months. There is precedence to this approach, especially in children where the developmental milestones/neurodevelopment are judged from memory based on how an individual child performed at different time points in their developmental life.^17–20^
If the child was seen in Acquired Brain Injury/Neurology/Neuro-psychology/Neurodevelopmental clinic at a specific site, the local research team will review the clinic letters/notes to ascertain child’s outcome as close as possible to 12 months from the head injury.

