### Statistics

#### Power calculation

The sample size has been calculated assuming a mean (±SD) PRx of 0.03±0.13 in patients with favourable outcome and a mean (±SD) PRx of 0.10±0.17 (SD) for patients with unfavourable outcome (from our previous work).^6^ For a one-sided analysis, using a favourable/unfavourable ratio of 0.77, with 80% power and alpha error of 5%, and allowing for losses (protocol violations, withdrawal of consent or lost to follow-up) the study will require 135 patients. Recruiting 135 patients with severe TBI in 36 months should have been feasible as based on the national audits of PICU (PICAnet report 2015: 188, 210, 211 patients in 2013, 2014 and 2015, respectively, with ICP devices from the 10 UK centres recruiting into the current study) and major trauma (TARN report on 2 years of severe injury in children (2013–2014): 1018 children in 2 years with severe head injury) with an estimated recruitment rate of 5–7 patients per site per year. On the basis of hospital episode statistics and data from the ongoing local severe TBI audit, approximately 5–10 patients with severe TBI are admitted in a medium-sized PICU each year.

However, due to the COVID-19 pandemic, the recruitment has been slow (pause of non-COVID-19 research projects, research staff redeployment to clinical work and lockdowns leading to changes in trauma patterns in children), and the study has been extended until December 2024 in agreement with the sponsor and funding organisation.

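### The mean-PRx comparison by outcome group that justifies 135 patients is not listed in the analysis section, whose two-group tests are defined on survival

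*Protocol article*

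**What the plan says.** All places are in the protocol article.

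- **Study objectives:** "Primary objective: To detect thresholds of PRx associated with favourable outcome in PTBI".
- **Outcome measures:** "The primary outcome will be measured by Glasgow Outcome Scale Extended Paediatric version (GOSE-Peds) at 12-month postinjury against the PRx". Mortality is listed among the secondary outcomes.
- **Power calculation:** the planning values are "mean (±SD) PRx of 0.03±0.13 in patients with favourable outcome" and "a mean (±SD) PRx of 0.10±0.17 (SD) for patients with unfavourable outcome". The design settings are "For a one-sided analysis, using a favourable/unfavourable ratio of 0.77, with 80% power and alpha error of 5" per cent. The total follows: "allowing for losses (protocol violations, withdrawal of consent or lost to follow-up) the study will require 135 patients". No loss rate is given.
- **Statistical analysis:** "Differences in physiological values between survivors and non-survivors will be interrogated with the Mann-Whitney U test for non-normally distributed continuous variables". The same sentence assigns Student's t-test to normally distributed variables and Fisher's exact test to categorical ones. No other pair of groups is named for these tests. The section then makes every test two-sided without multiplicity adjustment. It plans an iterative chi-square search for PRx cut-points that predict unfavourable outcome. It also plans ordinal logistic regression of GOSE-Peds on each monitored variable, adjusted for monitoring length and start day.

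**The concern.** A sample size should be traceable to an analysis that the plan commits to. Here the 135 comes from a difference in mean PRx between two outcome groups, and no listed analysis makes that comparison. The two-group tests that are listed use survival, which belongs to a secondary outcome and divides the cohort differently: children who survive with an unfavourable outcome are placed with those who recover well.

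Two things are at stake. First, a reader of the results could take a PRx comparison by survival for the comparison the study was powered on. Second, if the comparison by outcome group is run later, as seems likely, it will look post hoc although it is the basis of the design.

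This is not a detail the article leaves to a fuller document. It does name groups and tests, and the groups differ from those in its own sample-size calculation.

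**Working it through.** **Step 1. Reproduce the stated sample size.**

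Inputs from the Power calculation: means 0.03 and 0.10, so the difference is 0.07; SDs 0.13 (favourable) and 0.17 (unfavourable); favourable/unfavourable ratio 0.77; one-sided alpha 5%; power 80%.

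Formula for two means with unequal variances (normal approximation):

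n_unfav = (z_0.95 + z_0.80)² × (0.17² + 0.13²/0.77) / 0.07²

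- (1.645 + 0.842)² = 6.18
- 0.0289 + 0.0169/0.77 = 0.0508
- 6.18 × 0.0508 / 0.0049 = 64.2, rounded up to 65 unfavourable
- 0.77 × 65 = 50 favourable
- Total: 115 evaluable

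The Welch t version also gives 115. Inflating by 115/(1 − loss) gives:

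| Assumed loss | Recruits needed |
|---|---|
| 5% | 122 |
| 10% | 128 |
| 15% | 136 |
| 20% | 144 |

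The loss that gives exactly 135 is 1 − 115/135 = 14.8%. So 135 is consistent with a one-sided comparison of mean PRx by outcome group, on a back-solved loss of about 15%.

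**Step 2. Look for that comparison in the analysis section.**

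| Planned analysis | Outcome used | The comparison behind 135? |
|---|---|---|
| Mann-Whitney, Student's t, Fisher | Survival | No: different groups |
| Iterative chi-square over PRx cut-points | Unfavourable outcome | No: a cut-point search, not a difference in means |
| Ordinal logistic regression | GOSE-Peds | No: a different, adjusted model |

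The last two rows bear on the primary objective and the primary outcome. None of the three is the two-mean comparison.

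**Step 3. Are the two splits interchangeable?**

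The planning ratio makes 65/115 = 56.5% of children unfavourable. The survival split would match this only if essentially every unfavourable outcome were a death.

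**Step 4. Power of the comparison once it is listed.**

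With 65 and 50 children, SE = √(0.17²/65 + 0.13²/50) = √(0.000445 + 0.000338) = 0.0280, and 0.07/0.0280 = 2.50.

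- One-sided: Φ(2.50 − 1.645) = 0.80
- Two-sided: Φ(2.50 − 1.960) = 0.71

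The noncentral t (Welch) gives 0.80 and 0.70. Over a range of losses from 135, by the same method:

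| Evaluable | Loss from 135 | One-sided | Two-sided |
|---|---|---|---|
| 135 | 0% | 0.85 | 0.77 |
| 128 | about 5% | 0.84 | 0.75 |
| 115 | about 15% | 0.80 | 0.70 |
| 108 | 20% | 0.78 | 0.67 |

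A two-sided test with 80% power needs 82 + 63 = 145 evaluable (147 by the t version). That already exceeds 135 before losses; with 15% loss it is 145/0.85 = 171.

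**The case against.** The strongest reply is that the primary question is analysed. The threshold search addresses the primary objective directly, and the ordinal model relates PRx to GOSE-Peds without merging disabled survivors with good recoveries. The article never calls the survival comparison primary; it reads as a general description of physiological values. All of this stands. A reader might infer that PRx is never tested against favourable versus unfavourable outcome, or that the main result rests on mortality. The documents support neither reading.

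The reply does not supply a listed analysis that matches the 135. The chi-square search picks a cut-point from repeated, unadjusted tests, and the ordinal model was not sized.

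A reader might also want a figure for the power lost by splitting on survival, or for the type I error of Student's t under that split. The documents cannot give one. Mortality is not stated, nor is PRx in children who die. Carrying the 0.07 difference and the SDs of 0.13 and 0.17 over to survivors and non-survivors would not be coherent, because survivors would mix favourable and unfavourable children and so would have neither the favourable group's mean nor its SD. On the planning values, the more realistic survivor SD is about 0.15 to 0.16. No such figure is relied on here.

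Finally, the Power calculation names neither a scale nor a time point for its outcome groups. Reading them as 12-month GOSE-Peds is an inference from Outcome measures, where it is the only primary outcome.

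**Conclusion.** The point holds as a mismatch between the design and the listed analyses. The two-mean PRx comparison by outcome group that justifies 135 is absent, and the two-group tests use survival instead. It does not mean that the primary objective goes unanalysed.

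The size that can be established concerns the missing comparison itself: about 80% power one-sided and about 70% two-sided at 115 evaluable children. This rests on the article's planning means, SDs and ratio, and on an assumed loss of about 15%. If nobody were lost, two-sided power would still be about 77%. Adding the comparison under the present two-sided rule would therefore not restore the stated 80%, so the sidedness has to be settled in the same edit.

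**What to change.** In Statistical analysis, replace the survivor/non-survivor sentence with wording such as:

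> PRx will be compared between children with favourable and unfavourable GOSE-Peds at 12 months, using the Welch t-test or, if PRx is not normally distributed, the Mann-Whitney U test. This is the comparison on which the sample size is based. Survivors and non-survivors will be compared as a secondary analysis.

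Use the same favourable/unfavourable division as the threshold search, and name it in the Power calculation.

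Then reconcile the sidedness in one of two ways:

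- exempt this one test from the two-tailed rule and declare it one-sided at 5%, as the Power calculation assumes; or
- keep it two-sided and restate the power as about 70% at 115 evaluable children, giving the assumed loss rate.

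The cost is a few sentences in the analysis plan, ideally dated before the outcome data are analysed. It needs no further patients or measurements. Additional recruitment would arise only if the sponsor chose to keep 80% power with a two-sided test.

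### PRx thresholds, the primary objective, are sought by repeated χ² tests declared unadjusted; if the strongest cut is kept with its nominal p-value, the error rate is well above 5%

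*Protocol article*

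**What the plan says.** Under Study objectives: "Primary objective: To detect thresholds of PRx associated with favourable outcome in PTBI". Under Outcome measures: "The primary outcome will be measured by Glasgow Outcome Scale Extended Paediatric version (GOSE-Peds) at 12-month postinjury against the PRx". The abstract describes the first phase as powered for optimal PRx thresholds.

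Under Statistical analysis, the one method that yields a threshold is this: "Identification of critical threshold values of PRx for predicting unfavourable outcome will be performed using iterative" χ² tests, following a cited method. The general rule for testing, in the same paragraph, is "All tests will be two tailed and unadjusted for multiple comparisons". An ordinal logistic regression of GOSE-Peds on each monitored variable is also planned, with length of monitoring and day of starting monitoring as covariates.

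The sample size rests on a different analysis, a comparison of mean PRx between outcome groups: "a mean (±SD) PRx of 0.03±0.13 in patients with favourable outcome" against "a mean (±SD) PRx of 0.10±0.17 (SD) for patients with unfavourable outcome". It continues "For a one-sided analysis, using a favourable/unfavourable ratio of 0.77, with 80% power and alpha error of 5" per cent, and concludes that, "allowing for losses (protocol violations, withdrawal of consent or lost to follow-up) the study will require 135 patients".

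**The concern.** An iterative search tests the same outcome split at many PRx cuts. The largest χ² from such a search does not follow the χ² distribution on 1 degree of freedom, so comparing it with 3.84 does not give a 5% test. The unadjusted rule is a positive statement that covers every test, including this one, so the issue is more than detail left to another document.

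Two things are at stake. A threshold could be called significant when PRx carries no information about outcome. And because the same patients choose and evaluate the cut, any odds ratio, sensitivity or specificity quoted at it would be too favourable, while a single reported value would hide how much it could have moved.

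**Working it through.** **1. Inputs from the protocol (Power calculation).** Favourable: mean 0.03, SD 0.13. Unfavourable: mean 0.10, SD 0.17. Ratio 0.77, one-sided alpha 5%, power 80%, total 135 including losses.

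**2. Reproducing 135.**

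n(unfavourable) = (1.645 + 0.842)² × (0.17² + 0.13²/0.77) / 0.07² = 6.183 × 0.05085 / 0.0049 ≈ 64.2, so 65.

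n(favourable) = 0.77 × 64.2 ≈ 49.4, so 50. Total 115 evaluable.

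115/135 = 0.852, so 135 is reproduced with about 15% loss (the percentage is not stated; this is an assumption). The figure is sound for a one-sided comparison of two means. It does not describe the threshold search. The checks below use N = 115 and N = 135.

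**3. Error rate of an uncorrected scan.** Assumptions not in the document: cuts from -0.35 to 0.50, the steps shown, the minimum group sizes shown, and selection of the cut with the largest χ². PRx was drawn from the two distributions above and permuted against outcome, so that no association exists. The result is the proportion of simulated studies in which at least one cut has χ² > 3.84.

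| Step | ≥5 per side | ≥10% per side | ≥10% per side, continuity-corrected |
|---|---|---|---|
| 0.1 | 22-23% | 16% | 9-11% |
| 0.05 | 31-33% | 22-24% | 14-15% |
| 0.01 | about 48% | about 36% | 23-24% |

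Continuity correction with either minimum group size gives about 9-28% over these steps. Outside these grids, and without continuity correction, quartile cuts alone give 12-14% and scanning every observed value gives 57-61%. All these settings exceed 5%.

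**4. Cross-check by formula.** For a scan of every value between the 10th and 90th percentiles, the asymptotic approximation for a maximally selected χ², with z = 1.96, normal density φ(z) = 0.0584 and ε = 0.10, is

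P ≈ φ(z)(z − 1/z) ln[(1−ε)²/ε²] + 4φ(z)/z = 0.0584 × 1.450 × 4.394 + 4 × 0.0584/1.96 ≈ 0.372 + 0.119 = 0.49.

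Simulation of the same scan at these sample sizes gives 42-43%, so the order of magnitude is confirmed.

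**5. Critical value.** To hold 5%, the maximum χ² must exceed about 5.8-8.5 without continuity correction, depending on step and minimum group, instead of 3.84.

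**6. Stability and optimism.** With the protocol's two PRx distributions taken as true, N = 135, steps of 0.05 and at least 5 per side, the selected cut has percentiles (2.5/25/50/75/97.5) of -0.05/0.10/0.15/0.25/0.30. The range crosses zero, the value at which the Introduction separates intact from disturbed reactivity. With no association at all, the median odds ratio at a cut found significant is still about 3.2-3.6 (expressed as 1 or above).

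**The case against.** Four points are fair.

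- **No single false-positive rate belongs to this plan.** A reader might infer a fixed figure of 30-48%. The article gives no grid, range, minimum group or continuity correction, and that band arises only for steps of 0.05 to 0.01 with small permitted groups and the uncorrected statistic. A coarser or better protected scan gives much less. This stands, and the rate is therefore stated conditionally.
- **The selection rule is inferred.** The article does not say that the cut with the largest χ² is kept, nor that its p-value will decide whether PRx relates to outcome, nor that an odds ratio or accuracy figure will be given at the cut. The cited method is not shown. This stands. Keeping the strongest cut is the natural reading of an iterative search for a critical value, but it remains a condition of the finding.
- **Association is assessed elsewhere.** The ordinal regression relates PRx to GOSE-Peds without a selected cut. That is a real safeguard for the general question of association. It neither locates nor validates a threshold, so it does not cover the primary objective.
- **The article is condensed.** A reader might infer that no interval or internal validation is planned. The full protocol and any analysis plan are not shown, so silence on these is not a finding. What the article does state is that tests are unadjusted.

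The study is also observational, and its first step is described as retrospective analysis. That limits the immediate consequences but does not make the error rate right for an objective the abstract calls powered.

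**Conclusion.** Wrong as written. The stated rule that tests are unadjusted, applied to the only threshold method given for the primary objective, does not give a 5% error rate if the strongest cut is reported with its nominal p-value. The inflation is about two-fold in the most protected scan tabulated (10% minimum group, 0.1 steps, continuity correction) and more than nine-fold in the least protected (0.01 steps, 5 per side). These sizes rest on normal PRx with the protocol's means and SDs, 115 to 135 evaluable patients, and grids assumed for the calculation. The direction does not depend on the grid: every uncorrected scan examined exceeded 5%. The instability of the cut is a separate consequence, and it holds even if PRx truly differs between groups as the sample size assumes.

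**What to change.** Keep the iterative χ² scan as the search, and add to the analysis text:

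1. Fix the PRx grid and a minimum group fraction (for example 10%) before outcome data are examined, and state whether continuity correction is used.
2. Take the p-value for the threshold from the permutation distribution of the maximum χ² over that grid.
3. Exempt this analysis from the statement that tests are unadjusted.
4. Report a bootstrap 95% confidence interval for the threshold, repeating the whole search in each resample.
5. Give optimism-corrected values for any odds ratio, sensitivity or specificity quoted at the cut.

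The cost is a few lines of wording and a short program, with no new data or patients. The downside is larger p-values and a visibly wide interval. In simulations over a range of plausible grids, without continuity correction and with the protocol's assumed PRx distributions, the corrected scan had power of about 64-69% at 115 evaluable patients and 73-77% at 135. The stated 80% should therefore not be presented as the power for detecting a threshold.

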### Study aim

We aim to create a research database of high-resolution monitoring data from PTBI patients along with the clinical and demographic details and neuropsychological outcome up to 12 months postictus, from 10 UK PICUs to be used for research purposes. As the first step, we will analyse the data to determine retrospective optimal clinical parameters when managing these patients. Our hypothesis is that we can define the optimal parameters for CPP based on indices of autoregulation (PRx) and that the optimal parameters of CPP and PRx in PTBI will differ to adults, both qualitatively and quantitatively.

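### The iterative chi-squared search selects a PRx cut whether or not risk has a step, so the selected value alone does not show a critical threshold

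*Protocol article*

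**What the plan says.** Under Study objectives the primary objective is "To detect thresholds of PRx associated with favourable outcome in PTBI". Under Statistical analysis the method for it is given as "Identification of critical threshold values of PRx for predicting unfavourable outcome will be performed using iterative" chi-squared tests, after a cited method. The same paragraph makes all tests two-tailed, with no adjustment for multiplicity. It also plans an ordinal logistic regression of GOSE-Peds on each monitored variable. The purpose given is to allow for length of monitoring and the day monitoring began, not to check the cut.

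The Power calculation assumes "a mean (±SD) PRx of 0.03±0.13 in patients with favourable outcome" and "a mean (±SD) PRx of 0.10±0.17 (SD) for patients with unfavourable outcome", with a favourable/unfavourable ratio of 0.77. The Study aim hypothesises that "the optimal parameters of CPP and PRx in PTBI will differ to adults".

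**The concern.** A search that keeps the cut with the largest chi-squared value has a winner in any data set. A step in risk, a gradual curve and pure noise all produce one. A significant association between PRx and outcome is therefore not evidence that risk changes at the selected value.

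This affects what the primary result means. A cut reported as critical or optimal would be read as a value at which risk changes, and could be set beside adult values to address the Study aim. If risk is graded, the location of the cut reflects the shape and mix of the two PRx distributions and carries wide sampling error. A difference between two cohorts' cuts could then arise with no difference in where, or whether, risk changes.

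**Working it through.** **Inputs (Power calculation).** Favourable: mean 0.03, SD 0.13. Unfavourable: mean 0.10, SD 0.17. Ratio 0.77, so the unfavourable share is π = 1/1.77 = 0.565. One-sided 5%, power 80%, total 135. Assumptions: normal PRx within each group, one summary PRx per child, outcome dichotomised.

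**1. The plan's own figure.** Unequal-variance formula:
- n(unfavourable) = (1.645 + 0.842)² × (0.17² + 0.13²/0.77) / 0.07² = 6.183 × 0.05085 / 0.0049 = 64.2, so 65.
- n(favourable) = 0.77 × 64.2 = 49.4, so 50. Total 115.
- A pooled SD gives 119 and a t-based calculation 121.
- The loss rate is not stated. Assuming 10% to 15%, 121/0.90 = 134.4 and 115/0.85 = 135.3, so 135 is reproduced.

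This is a comparison of two means. No search over cuts enters it.

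**2. Risk implied by the planning figures.** P(unfavourable | x) = π·f_u(x) / [π·f_u(x) + (1−π)·f_f(x)], where f_u and f_f are the two normal densities. At x = 0.20: 0.565 × 1.974 / (0.565 × 1.974 + 0.435 × 1.305) = 0.66.

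| PRx | -0.30 | -0.07 | 0 | 0.10 | 0.20 | 0.30 |
|---|---|---|---|---|---|---|
| Risk | 0.61 | 0.45 | 0.46 | 0.53 | 0.66 | 0.81 |

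The minimum is where (x − 0.03)/0.13² = (x − 0.10)/0.17², that is x = -0.069. The curve is smooth, has no step, and does not rise throughout.

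**3. Where the search lands in a very large sample.** For a cut c, φ²(c) = π(1−π)(F_u − F_f)² / [F(1−F)], where F_u, F_f and F are the proportions below c in the unfavourable group, the favourable group and overall.
- Stated SDs: the maximum is at c = 0.183, where F_u = 0.687, F_f = 0.880, F = 0.771 and φ² = 0.2458 × 0.0373 / 0.1764 = 0.052. At the cohort mean (0.565 × 0.10 + 0.435 × 0.03 = 0.070) φ² is 0.036.
- Common SD of 0.153, same means: the maximum is at c = 0.058.

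Neither case has a step. The cut still moves by 0.183 − 0.058 = 0.125, about 1.8 times the planned difference of 0.07.

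**4. Precision at the planned size.** Simulation from the planning figures, keeping the largest chi-squared value:
- 135 children, every observed cut, at least 12 per side: median cut 0.165, 95% range -0.04 to 0.29.
- 115 children, cuts every 0.05, at least 5 per side: 95% range about -0.10 to 0.30.
- In 115 to 135 children on that same grid, the selected cut was nominally significant in about 93% to 96% of runs. The association is real in these runs, but there is no step.
- With no association at all, the selected cut was nominally significant in about 30% of runs on that grid. Over other settings this was 23% to 37% for a 0.05 grid and 44% to 61% for every observed cut.

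**5. Does the cut follow the cohort mean?** With one fixed linear-logit risk curve, yes: cohort means of -0.05, 0.07 and 0.20 gave large-sample cuts of about -0.04, 0.06 and 0.17. With the risk curve implied by the planning figures, hardly: the same shift in mean moved the cut only from 0.166 to 0.224. With the planning distributions held fixed, raising the unfavourable share from 20% to 80% raised the mean from 0.044 to 0.086 while the cut fell from 0.237 to 0.162.

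**The case against.** **The plan does not rest on the cut alone.** The primary outcome is GOSE-Peds against PRx, and ordinal regression and Spearman correlation are planned. This stands in part: a graded analysis exists and the fix builds on it. But its stated role is covariate adjustment, and nothing links it to whether a threshold exists.

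**The article is condensed.** The full protocol, any SAP and the cited method are not shown. They may set a grid, a minimum group size, a significance requirement or a validation step. This also stands in part: if significance is required, some data sets would yield no cut. It does not remove the point, because the article itself names the search as the method for its primary objective, and significance at a cut is not evidence of a step.

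**The word threshold may mean only a prognostic cut.** The article nowhere says that risk has a step or calls the cut a physiological limit, and the study is observational. That is fair, and it makes the matter one of interpretation and reporting. The words critical and optimal still invite the stronger meaning.

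**A stronger reading is tempting.** A reader might infer that, on the plan's own figures, the cut simply lands near the cohort's average PRx and moves with it. The document does not support that. With the stated SDs of 0.13 and 0.17 the large-sample cut is 0.183 against a mean of 0.070, about 0.7 SD higher. Following the mean needs an approximately linear logit or roughly equal SDs, and neither is in the plan.

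**Conclusion.** The concern holds in this form: the search selects a PRx cut whether or not risk has a step, so the selected value alone does not establish a critical threshold. On the planning figures, which contain no step, it would centre at about 0.15 to 0.18 with a 95% range of roughly -0.10 to 0.30 at 115 to 135 children. Its location depends on the shape of the two PRx distributions.

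This rests on normal PRx within groups, one PRx summary per child, a dichotomised outcome and selection of the largest chi-squared value. The grid and minimum group size are also assumed, since the article does not give them. The exact range shifts with those choices; the conclusion does not. It should be settled before analysis because it determines what the primary result can claim.

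**What to change.** - In the ordinal regression already planned, model 12-month GOSE-Peds on continuous PRx, for example with a restricted cubic spline of 3 to 4 knots. Report the risk curve with its confidence band as the main result.
- Report the iterative chi-squared cut as descriptive, with a bootstrap interval that repeats the whole search and a p value corrected for the search.
- Do not call the cut critical or optimal unless a step-versus-smooth comparison supports a step. Treat that comparison as supportive, because it has little power at 115 to 135 children. It should not decide whether the cut is reported at all.

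The cost is a change of wording in the analysis plan and a little more analysis, with no new data. The downside is that the study may have to report graded risk, or a cut with a wide interval, in place of a single threshold.
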